## Abstract

**Background::**

In clinical practice, laboratory results are often important for making diagnostic, therapeutic, and prognostic decisions. Interpreting individual results relies on accurate reference intervals and decision limits. Despite the considerable amount of resources in clinical medicine spent on elderly patients, accurate reference intervals for the elderly are rarely available. The SENIORLAB study set out to determine reference intervals in the elderly by investigating a large variety of laboratory parameters in clinical chemistry, hematology, and immunology.

**Methods/design::**

The SENIORLAB study is an observational, prospective cohort study. Subjectively healthy residents of Switzerland aged 60 years and older were included for baseline examination (n = 1467), where anthropometric measurements were taken, medical history was reviewed, and a fasting blood sample was drawn under optimal preanalytical conditions. More than 110 laboratory parameters were measured, and a biobank was set up. The study participants are followed up every 3 to 5 years for quality of life, morbidity, and mortality. The primary aim is to evaluate different laboratory parameters at age-related reference intervals. The secondary aims of this study include the following: identify associations between different parameters, identify diagnostic characteristics to diagnose different circumstances, identify the prevalence of occult disease in subjectively healthy individuals, and identify the prognostic factors for the investigated outcomes, including mortality.

**Discussion::**

To obtain better grounds to justify clinical decisions, specific reference intervals for laboratory parameters of the elderly are needed. Reference intervals are obtained from healthy individuals. A major obstacle when obtaining reference intervals in the elderly is the definition of health in seniors because individuals without any medical condition and any medication are rare in older adulthood. Reference intervals obtained from such individuals cannot be considered representative for seniors in a status of age-specific normal health. In addition to the established methods for determining reference intervals, this longitudinal study utilizes a unique approach, in that survival and long-term well-being are taken as indicators of health in seniors. This approach is expected to provide robust and representative reference intervals that are obtained from an adequate reference population and not a collective of highly selected individuals.

**Trial registration::**

The present study was registered under International Standard Randomized Controlled Trial Number registry: ISRCTN53778569.

## Background

1

In clinical medicine, decisions are often made based on patient history and examination results. Based on such types of information, prognosis and disease course can be estimated, and treatment decisions can be made.^[1]^ Within this context, laboratory medicine frequently provides important supportive information, on which decisions are based. In approximately 50% to 79% of hospitalized patients or outpatient cases from general internal medicine providers, laboratory measurements play a decisive role when planning the treatment course for the patient.^[2–4]^

Laboratory test results are interpreted in the context of clinical information by comparison with reference intervals and longitudinal interpretation of sequential results.^[5–7]^ These reference intervals are most often obtained from investigations in healthy adult persons aged <60 years.^[8,9]^ Although elderly persons sometimes are regarded as elderly versions of adults, from a physiopathological viewpoint, seniors—analogously to children—have their distinct own biology. Despite this, reference intervals obtained from young and healthy persons are often used in elderly patients.^[10–12]^

The importance of building reliable and robust reference intervals in laboratory parameters has recently gained increasing attention.^[13]^ In 2005, the International Federation of Clinical Chemistry and Laboratory Medicine founded a working group on reference ranges, and its publications have laid a foundation for the investigation of reference intervals.^[13–15]^ Although the majority of health care resources are spent on the elderly, reference ranges for the elderly are scarce. Thus far, with the exception of the very recently published data obtained within the framework of the Canadian Health Measures Survey,^[16–18]^ few studies have aimed to define normal ranges for the most common analyses, which included <40 parameters in each study.^[19–26]^ Some of this scientific work has been published >20 years ago and has been conducted in relatively small cohorts. As a major drawback of these studies, the employed laboratory methods cannot be traced to reference methods or are not in use anymore. Furthermore, all of these investigations are cross-sectional in nature. Accordingly, the usefulness of the reference intervals of the reported parameters can be considered to be limited.

Wrong interpretation of laboratory test results due to the use of unsuitable reference ranges leads to false-negative and false-positive results. False results are a major source of harm in a patient. Time-consuming and worrying test procedures are too often performed in medicine to substantiate (false) positive findings. These procedures are not only burdensome for the patient and his or her family caregivers but also a major cause of unnecessarily expenses. At the end of life, the aim is to limit medical procedures to the minimum. Unnecessary procedures in this phase of life can be considered unethical because they put an unnecessary burden on the shoulders of a patient whose life should be made as comfortable as possible. As long as clinical medicine uses inappropriate reference intervals for the elderly, unnecessary procedures may be commonly ordered. More appropriate reference intervals are expected to reduce the frequency of potentially humiliating medical procedures during the last phase of life.^[1]^

To obtain better grounds on which to base clinical decisions, specific reference intervals for frequently used laboratory parameters of the elderly are urgently needed.^[10–12]^ The present study protocol presents the SENIORLAB study as an investigation with an extensive examination of study participants at baseline and, as a further unique feature of this study, a longitudinal follow-up.

The study setting allows for work on several aims and investigation of a multitude of research questions. The primary aim is to establish robust reference intervals for >110 different parameters in subjectively healthy elderly persons who demonstrated survival at the follow-up examinations. This additional methodological strength of the SENIORLAB study is unprecedented and has the potential of modifying the theory of constructing reference intervals within the senior citizen community. The secondary aims of the SENIORLAB study are as follows: to test the diagnostic characteristics of certain laboratory parameters (e.g., red blood cell characteristics) and to characterize biochemically defined disorders such as vitamin B_12_ deficiency, which can also occur in a subjectively healthy elderly cohort (this approach may help identify novel markers for more efficient identification of common disorders among the elderly population); to investigate associations of different biomarkers with other biomarkers (this approach helps to better understand the pathophysiology and behavior of the different laboratory parameters in seniors and may ultimately lead to a better interpretation of laboratory results, preventing false-negative and false-positive diagnosis in elderly patients with the subsequent consequences); to investigate the prevalence of occult and early disease in subjectively healthy elderly persons (e.g., type 2 diabetes mellitus, thyroid disease, vitamin deficiency, renal disease) (some disorders are exclusively diagnosed by laboratory parameters; this approach helps estimate the magnitude of relevant underdiagnosed diseases in the elderly and may help shape policies regarding better and earlier detection for earlier intervention); and to investigate risk factors for the loss of subjective well-being, mortality, hospitalization, and impaired autonomy among the elderly. Identifying these factors may help identify elderly individuals who may appear healthy but require closer medical attention and may benefit from medical interventions.

## Methods/design

2

### Study design

2.1

Reporting the design of this study strictly follows the STROBE statement, except for the guidelines in results and discussion sections because this report is a study protocol.^[27]^ The research project is designed as a prospective, single-center, cohort study with an extensive baseline examination and a periodic longitudinal follow-up. The current article provides a comprehensive synopsis for the main design of the SENIORLAB study, including a report on participant recruitment, baseline examinations, and follow-up.

### Setting

2.2

The study was initiated by a medical laboratory and aimed to recruit study participants in the community. The location and organization of the study center is associated with the laboratory, which is located in Berne in the midlands of Switzerland. For the baseline examination, study participants were recruited from May 2009 to December 2011. Follow-up examinations are planned every 3 to 5 years. The first follow-up was done from December 2013 to December 2014. The second follow-up investigation is scheduled for October 2017 to October 2018. The study is registered in the International Standard Randomized Controlled Trial Number registry (ISRCTN53778569), where all items of the World Health Organization (WHO) Trial Registration Data Set have been specified.

### Ethics, consent, and permissions

2.3

The study was approved by the Ethics Committee Bern (Kantonale Ethikkommission Bern; ref 166/08) on January 5, 2009, and an amendment regarding the prospective study was approved on July 29, 2013. Study participants provided written informed consent before entering the study.

### Participants

2.4

Consecutive, subjectively healthy elderly volunteers aged 60 years and older were recruited. The study participants were contacted through newspaper advertisements, various clubs, and at associations that had high proportions of healthy elderly members (e.g., alpine clubs and sports clubs). In addition, participants were recruited through personal contacts of the collaborators of the study organization. Inclusion criteria were as follows: age 60 or older, residence in Switzerland, the subjective perception of being healthy, and being in a fasting state at the baseline examination. Exclusion criteria were as follows: known diabetes mellitus, known thyroid disease, current glucocorticoid use, active neoplastic disease during the past 5 years, consumption of >5 pharmacologically active substances (polypharmacy), and hospitalization during the past 4 weeks. Study participants and their primary care physicians, as requested, were given the results of selected values that are widely screened in asymptomatic healthy individuals, such as fasting glucose, total cholesterol, creatinine, hemoglobin, red blood cells, white blood cells, and thrombocytes. For the follow-up examinations, study participants are contacted by letter and telephone. In the case of a participant's lack of response, official communal authorities, relatives, and/or neighbors are contacted to obtain the study participant's information.

### Data collection and measurements

2.5

Each participant's personal history and anthropometric measurements, such as height and weight, were obtained. Histories of participants were obtained using questions including whether a participant considered himself or herself as healthy and believed to have an intact cognitive state. Furthermore, a personal history of diseases and surgical procedures, as well as intake of drugs and supplements, was recorded. Blood pressure was measured in a standardized manner in a seated position after a 10-minute rest. Venous blood was drawn into S-Monovette (Sarstedt, Sevelen, Switzerland) after an overnight fasting period. The laboratory samples were processed (i.e., centrifuged, aliquoted, and analyzed or frozen at −80°C) immediately after the blood was drawn to allow for standardized preanalytics. In the follow-up surveys, information on subjective well-being, mortality, reason of death, hospitalization, and impaired autonomy is recorded.

The investigators will have access to the final dataset. For qualified analysis plans, they will provide data access to qualified scientists. The data monitoring committee consists of the 3 study investigators and ascertains integrity as well as correctness of data and analyzed and handled adverse events and other unintended effects. This was done after the baseline examination and will be continued after each follow-up period. Follow-up will be performed until funds are available. Confidentiality of data is protected before, during, and after the trial.

Laboratory parameters were measured on up-to-date diagnostic platforms from different manufacturers (e.g., Roche Diagnostics, Abbott Diagnostics, Siemens, Beckmann Coulter, Sysmex) and also by employing, for example, open immunoassay platforms or high-performance liquid chromatography-tandem mass spectrometry instruments. The laboratory analyses were performed according to the requirements of the Swiss commission for quality assurance in the medical laboratory. For internal quality control, commercially available control materials were used when available. The investigated parameters, together with manufacturer and imprecision, are provided in Table 1  . If available, aliquots of each sample were stored at −80°C. This step allows for the analysis of additional parameters of interest. The freezers used to store the samples have been continuously monitored for an adequate temperature.

**Table 1 T1:**
[figure not shown]
Employed laboratory methods with their imprecision at different concentration levels.

**Table 1 (Continued) T2:**
[figure not shown]
Employed laboratory methods with their imprecision at different concentration levels.

**Table 1 (Continued) T3:**
[figure not shown]
Employed laboratory methods with their imprecision at different concentration levels.

### Sample size

2.6

The Clinical Laboratory Standards Institute (CLSI) released a relevant guideline (C28-A3c) for the evaluation of reference intervals.^[15]^ There are several possibilities to evaluate reference intervals. The most commonly stated minimal number of included subjects is 120 per stratum. This number allows for determination of the 90% confidence interval of the upper and lower reference limits. However, the so-called robust method also offers the possibility to evaluate reference intervals with fewer individuals. We anticipated age and gender stratification. For age stratification, we collapsed the participants to 5-year age cohorts (e.g., age 60–64, 65–69, 70–74). We aimed to include at least 120 participants in the 5-year age cohorts. The recruitment for an age stratum was stopped if >200 participants were already included in the respective stratum.

### Analysis plan

2.7

An overview on participant enrollment, data acquisition, and data analysis is given in the flow diagram (see Fig. 1). Participants can be excluded at different stages of the study: before baseline examination or after the baseline visit. Clinicopathological measurements were conducted immediately after drawing the blood samples to provide optimal preanalytical conditions. Due to logistical reasons, it sometimes only became apparent that an exclusion criterion applied after clinicopathological measurements were conducted (e.g., in the case of consumption of a combination drug or in the case of the consumption of an antidiabetic medication in the absence of information that a participant suffers from diabetes, despite explicitly being asked about this condition). Together, 1467 individuals presented at the baseline visit. For the determination of reference intervals, participants lost to follow-up will not be included into the statistical analysis.

**Figure 1 F1:**
[figure not shown]
Study algorithm of the SENIORLAB study.

To evaluate reference intervals (primary aim) according to the CLSI C28-A3c guideline, laboratory parameters will be analyzed for partitioning factors (e.g., age, gender) by correlation in the case of continuous variables and by a statistical comparison of the means and medians in the case of binary variables. Outliers will be eliminated according to the method of Dixon and Reed or alternative methods.^[15]^ After an analysis of the normal distributions of the laboratory results, parametric or nonparametric reference ranges will be calculated. Should a stratum have fewer than 120 subjects, then the robust method will be applied. Judgment on whether the included number of study participants in a respective stratum is sufficient will be made by the method of Boyd and coworkers.^[15]^ Furthermore, age-related continuous reference intervals are calculated.^[28–30]^ The computer programs MedCalc (Mariakerke, Belgium) and StatisPro (CLSI, Wayne, PA) will be used for these calculations and analyses.^[15]^

For statistical analysis of the secondary aims, the following methods will be used: diagnostic characteristics will be evaluated by Receiver operating characteristic curve analysis, and sensitivity, specificity, predictive values, and likelihood ratios will be calculated (by looking at optimum decision concentrations and concentrations with high sensitivity and high specificity, this approach may be able to evaluate decision limits that identify persons with probable or improbable disease and describe a gray zone of diagnostic uncertainty)^[31]^; associations between different variables will be assessed by correlation and by univariate and multivariate linear regression analyses (the latter will represent a means to control for covariates, confounders, or potential bias; goodness of model fit, regression coefficients, and partial correlation coefficients will be evaluated in these models); descriptive statistics will be used to evaluate the frequency of occult disease; logistic regression analysis and longitudinal analysis will be employed to evaluate risks for the occurrence of outcomes.

For all other analyses, statistical comparisons will be performed by *t* test/Mann–Whitney *U* test, χ^2^ or Fisher exact test; tests for trend; or analysis of variance/Kruskal–Wallis test, as indicated by the specific statistical problem. The computer programs MedCalc (Mariakerke) and SPSS (IBM, Zurich, Switzerland) will be used for the analyses of secondary aims. Study results will be disseminated via publications. Authorship will be attributed according to the criteria issued by the International Committee of Medical Journal Editors. Data will be made accessible to other researches after data sharing arrangements could be met.

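### Partitioning is assessed by location only (correlation, means, medians), although the reference limits lie in the tails, so a sex difference in spread can go unseen

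*Protocol article*

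**What the plan says.** Section 2.7 (Analysis plan, text after Figure 1) opens "To evaluate reference intervals (primary aim) according to the CLSI C28-A3c guideline" and then writes out how partitioning is examined. For a continuous factor such as age, the method is given as "laboratory parameters will be analyzed for partitioning factors (e.g., age, gender) by correlation in the case of continuous variables". A factor with two levels, such as sex, is instead to be examined "by a statistical comparison of the means and medians in the case of binary variables". The section names no comparison of spread and no criterion on the limits themselves. It states no significance level and no minimum effect.

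The other method named nearby has a different job: "Judgment on whether the included number of study participants in a respective stratum is sufficient will be made by the method of Boyd and coworkers". That concerns stratum size, not whether to split.

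Section 2.7 also plans continuous age-related reference intervals, and section 2.6 says that age and gender strata were anticipated. On numbers, section 2.7 says "Together, 1467 individuals presented at the baseline visit" and "For the determination of reference intervals, participants lost to follow-up will not be included into the statistical analysis". The analysed number is therefore below 1467 by an amount the article does not give.

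**The concern.** A reference interval is defined by its outer percentiles, conventionally the 2.5th and 97.5th. Whether two groups can share an interval depends on whether those percentiles agree. Equal means and medians do not ensure that: if one sex has the wider distribution, common limits are too wide for the other sex and too narrow for it. One group then gets too few flags and the other too many. The Background names false-negative and false-positive results from unsuitable ranges as the harm the study is meant to reduce.

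The mismatch also runs the other way, though less firmly. In a large sample, a location test can be significant for a shift that leaves the limits almost where they were. A needless split costs precision. Section 2.6 aims for at least 120 per 5-year cohort and stops recruiting above 200, so splitting a cohort equally by sex gives about 60 to 100 per cell, below the 120 at which section 2.7 turns to the robust method.

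**Working it through.** **Inputs from the article.** Baseline N = 1467 (2.7); at least 120 per stratum (2.6); partitioning by correlation and by means and medians (2.7).

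**Assumptions not in the article.** Two-sided alpha 0.05; equal numbers of men and women; normal values unless stated; analysed N between 700 and 1467.

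**1. The plan's own figure.** Section 2.6 says "The most commonly stated minimal number of included subjects is 120 per stratum" and "This number allows for determination of the 90% confidence interval of the upper and lower reference limits". For a nonparametric 90% interval with 5% on each side, the smallest observation must lie below the 2.5th percentile with probability at least 0.95: 1 − 0.975^n ≥ 0.95, so n ≥ ln 0.05 / ln 0.975 = 118.3, i.e. 119. At n = 120 the probability is 0.952. The figure of 120 is reproduced, and it is a requirement on the tails. The partition step is not.

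**2. Equal centres, unequal spread.** Let group A be N(0, 1) and group B be N(0, r²), in equal numbers. The common limits ±c solve ½Φ(−c) + ½Φ(−c/r) = 0.025.

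- r = 1.25: c = 2.231. Per tail, A has Φ(−2.231) = 1.28% and B has Φ(−2.231/1.25) = 3.72%. Outside in total: 2.6% and 7.4%.
- r = 1.5: c = 2.549. Per tail, A has 0.54% and B has 4.46%. Outside in total: 1.1% and 8.9%.

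The nominal total is 5% in each group. B's own limits at r = 1.5 would be ±1.96 × 1.5 = ±2.94, not ±2.55.

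**3. What the stated comparison sees.** In 2,000 simulated data sets per setting, the Welch t test and the Mann-Whitney test rejected in about 4% to 6% of runs for both SD ratios, at every size from 60 to 733 per sex. More participants do not help. Levene's test of spread rejected in essentially all runs at r = 1.5 with 350 or more per sex, and in 97% or more at r = 1.25. The data would show the difference; the stated method does not look for it.

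**4. Skewed analytes.** With lognormal values, equal medians, a log-SD ratio of 1.5 and a Welch test on the raw scale, power is roughly:

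| log-SDs | 700 per group | 350 per group |
|---|---|---|
| 0.2 vs 0.3 | 44% | 23% |
| 0.3 vs 0.45 | 75% | 46% |
| 0.4 vs 0.6 | 93% | 65% |

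Here a spread difference moves the mean, so detection is partial.

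**5. Small shifts, if p < 0.05 is the trigger.** With equal SDs and a shift of 0.15 SD, the common limits are −1.89 and 2.04 in units of A. The tail shares are 2.93% and 2.07% in A, mirrored in B. Power is about Φ(0.15/√(2/n) − 1.96), with n per sex:

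- N = 1467 (n = 733): 82%
- N = 1000 (n = 500): 66%
- N = 700 (n = 350): 51%
- one 5-year cohort of 120 to 200 (n = 60 to 100): 13% to 18%

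**6. Age.** When the SD rises 1.5-fold across the age range with no trend in the mean, a correlation test rejected in about 5% to 6% of runs (N = 1467 and N = 1000). This is the same blindness, but continuous age-related intervals are planned alongside.

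**The case against.** The strongest reply is that section 2.7 only says how factors will be analysed. It does not say that a significant result triggers a split, and a correlation can be judged by its size. Operational thresholds may sit in a fuller plan. This stands against the small-shift argument, which needs an assumed 5% trigger and most of the cohort in one test. It does not touch the spread argument: whatever threshold is used, means, medians and a correlation describe location and trend.

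A second reply is that the work follows the CLSI guideline, which may contain a better criterion. The guideline's content is not in the article and cannot be relied on in either direction. The sentence that cites it goes on to write out a location-only method.

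Third, the 5% detection rate belongs to the symmetric case. This stands: for skewed analytes the mean comparison has some power, and the article shows no analyte with equal centres and an SD ratio of 1.5. The ratios are illustrations.

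Two stronger readings are tempting. A reader might multiply more than 110 parameters by two factors and 5% to predict a number of chance splits. The article states neither alpha nor a significance trigger, so that count has no basis in it. A reader might also say that correlation leaves non-monotone age effects undetected. The planned continuous age-related intervals and the anticipated 5-year strata mean that age limits do not rest on a correlation alone.

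**Conclusion.** The point holds in a limited form. The partition method written into section 2.7 targets location, while the result it governs is a pair of tail limits. For a binary factor, mainly sex, and a roughly symmetric analyte with equal centres, the spread difference is flagged only at the false-positive rate at any N. Common limits would then misstate the share outside as computed above, with the wider group at about one and a half times (7.4%) to nearly twice (8.9%) the nominal 5%. This needs no particular sample size; the percentages assume normal values and equal group sizes. For skewed analytes the gap is partial.

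Needless splitting on small shifts is a conditional secondary point. It depends on a 5% trigger and on how many participants remain after losses to follow-up, and it does not arise within a single 5-year cohort. For age, the weakness is partly relieved by the continuous intervals. The change is worth making because it replaces a stated method with one aimed at the right quantity, using data already collected.

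**What to change.** In section 2.7, base the partition decision on the limits. Either compute common limits and partition when a subgroup's share outside them departs from nominal by more than a pre-set margin, or use a Harris-Boyd type criterion that includes an SD-ratio check. Keep the correlation and the mean and median comparisons as descriptive screening.

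The cost is about one sentence and modest extra computation; no new data are needed. The drawback is noise in small subgroups. Treating the common limits as fixed, the standard error of a 2.5% tail share is √(0.025 × 0.975 / n): about 2.0 percentage points at n = 60, 1.4 at 120, 0.8 at 350 and 0.6 at 733. The margin must allow for this, and its choice matters. As an illustration, a per-tail range of 1% to 4% would catch the SD ratio of 1.5 (0.5% and 4.5%) but not 1.25 (1.3% and 3.7%). Setting it before the analysis, with the SD-ratio check beside it, keeps the decision from being made analyte by analyte.

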We expect the SENIORLAB study to provide insights on the influence of age on the behavior of laboratory parameters. Accordingly, we will be able to define accurate reference intervals and decision limits for a multitude of laboratory parameters, which constitute a great majority of clinically ordered laboratory test in senior citizens. From a methodological perspective, we will be able to include longitudinal follow-up as a relevant criterion to select appropriate individuals for the evaluation of reference intervals. This follow-up will be an important step in the theory and practice of defining reference intervals in the elderly.

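### As written, sensitivity at the ROC-derived optimum cut-off will be too favourable, by an amount that depends on an unstated number of cases

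*Protocol article*

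**What the plan says.** The Background lists, as a secondary aim, "to test the diagnostic characteristics of certain laboratory parameters (e.g., red blood cell characteristics"). Section 2.7 (Analysis plan, the text after Figure 1) gives the method: "diagnostic characteristics will be evaluated by Receiver operating characteristic curve analysis, and sensitivity, specificity, predictive values, and likelihood ratios will be calculated". Cut-offs are to be found "by looking at optimum decision concentrations and concentrations with high sensitivity and high specificity". Of what this may yield, the article says only that "this approach may be able to evaluate decision limits that identify persons with probable or improbable disease and describe a gray zone of diagnostic uncertainty". It does not name the criterion that makes a concentration optimal.

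Section 2.1 describes a single source of data: "The research project is designed as a prospective, single-center, cohort study with an extensive baseline examination and a periodic longitudinal follow-up". Section 2.7 gives its size: "Together, 1467 individuals presented at the baseline visit". Some exclusions came to light only after that visit, so 1467 is an upper bound for any analysis. No section names a split sample, a resampling step or a validation cohort. Section 2.6 sizes the study for reference intervals only. The closing paragraph of the Discussion is firmer than section 2.7 and expects to "define accurate reference intervals and decision limits for a multitude of laboratory parameters".

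**The concern.** An optimum cut-off is the point where the observed ROC curve looks best. That point partly reflects chance in the sample that produced the curve. If the same participants then supply the accuracy figures, the chance gain is counted as real performance. The smaller group, normally the cases, is the noisier one, so most of the gain falls on sensitivity.

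The Discussion has practical use in mind, namely screening elderly people for common deficiencies with blood indices. The Background names false-negative results among the harms that the study hopes to reduce. A screening limit published with overstated sensitivity would understate exactly those.

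**Working it through.** **The plan's own figure.** The article gives no number for the ROC analysis. Its only sample-size figure concerns reference limits: "The most commonly stated minimal number of included subjects is 120 per stratum". It reproduces. A nonparametric 90% confidence interval for the 2.5th percentile needs 0.975^n ≤ 0.05. Since 0.975^118 = 0.0504 and 0.975^119 = 0.0492, the minimum is 119. This has no bearing on ROC work.

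**Inputs.** N = 1467 comes from section 2.7. These are assumptions, because the article gives none of them:
- number of cases: 15, 29, 73, 147 or 293 (1%, 2%, 5%, 10%, 20%)
- AUC: 0.70 or 0.80
- marker distribution: normal with equal variance in cases and non-cases
- cut-off: the value that maximises J = Se + Sp − 1 (Youden)

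**Model.** The separation between groups is d = √2·Φ⁻¹(AUC). The best attainable cut-off is d/2, where Se = Sp = Φ(d/2).
- AUC 0.70: d = 1.414 × 0.524 = 0.742, so Se = Φ(0.371) = 0.645.
- AUC 0.80: d = 1.414 × 0.842 = 1.190, so Se = Φ(0.595) = 0.724.

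**Comparison.** In each of 3000 simulated data sets the cut-off c was chosen in the sample. Apparent Se is the sample proportion of cases at or above c. True Se is 1 − Φ(c − d). Apparent and true values:

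| Cases | AUC | Se apparent / true | Excess (points) | Sp apparent / true | Median LR+ apparent / true |
|---|---|---|---|---|---|
| 15 | 0.70 | 0.734 / 0.608 | 12.6 | 0.656 / 0.655 | 2.21 / 1.86 |
| 15 | 0.80 | 0.801 / 0.684 | 11.7 | 0.737 / 0.736 | 3.19 / 2.77 |
| 29 | 0.70 | 0.702 / 0.614 | 8.8 | 0.657 / 0.656 | 2.10 / 1.86 |
| 29 | 0.80 | 0.774 / 0.696 | 7.8 | 0.735 / 0.734 | 3.02 / 2.74 |
| 73 | 0.70 | 0.678 / 0.629 | 4.9 | 0.651 / 0.649 | 1.97 / 1.84 |
| 73 | 0.80 | 0.753 / 0.709 | 4.4 | 0.730 / 0.728 | 2.84 / 2.69 |
| 147 | 0.70 | 0.667 / 0.633 | 3.4 | 0.651 / 0.648 | 1.93 / 1.83 |
| 147 | 0.80 | 0.740 / 0.712 | 2.8 | 0.732 / 0.729 | 2.79 / 2.68 |
| 293 | 0.70 | 0.659 / 0.639 | 2.0 | 0.649 / 0.644 | 1.89 / 1.82 |
| 293 | 0.80 | 0.738 / 0.722 | 1.6 | 0.726 / 0.722 | 2.71 / 2.62 |

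Further runs of the same model give an excess of about 10 points with 20 cases and 6 to 7 with 40. LR+ is inflated by 15% to 19% with 15 cases (3.19/2.77 = 1.15; 2.21/1.86 = 1.19) and by 3% to 4% with 293 (2.71/2.62 = 1.03; 1.89/1.82 = 1.04).

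**What this does to the other measures** (73 cases, AUC 0.80, mean values from the table; 1467 − 73 = 1394 non-cases):
- Missed cases: 73 × (1 − 0.753) = 18.0 apparent; 73 × (1 − 0.709) = 21.2 true.
- LR− = (1 − Se)/Sp: 0.247/0.730 = 0.34 apparent; 0.291/0.728 = 0.40 true.
- PPV = TP/(TP + FP): 55.0/(55.0 + 376.4) = 12.7% apparent; 51.8/(51.8 + 379.2) = 12.0% true.

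**Gray-zone limits.** Section 2.7 also looks at concentrations with high sensitivity or high specificity. With targets of 95% (assumed) and AUC 0.80, apparent against true sensitivity at the high-sensitivity limit is 1.000 / 0.936 with 15 cases, 0.966 / 0.932 with 29, 0.959 / 0.946 with 73 and 0.952 / 0.949 with 293. Specificity at the high-specificity limit is 0.950 / 0.950.

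**Does bootstrap correction work?** At AUC 0.70 with 40 cases, mean J is 0.346 apparent, 0.295 corrected and 0.273 true. The share of optimism removed is (0.346 − 0.295)/(0.346 − 0.273) = 0.051/0.073 = 70%.

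**The case against.** The strongest reply is that the point rests on silence. Section 2.7 does not say that selection and evaluation share the same participants without correction. It does not exclude the bootstrap, cross-validation or later external validation, and it refers to a cited source for the method that is not at hand. A condensed article may leave such steps for an exploratory secondary aim to a fuller document. This stands to the extent that same-sample scoring is an inference, and it lowers the weight of the point. It does not remove it: the article spells out a procedure, describes one cohort and states no step that would undo the optimism. Following that procedure as written gives biased figures at the optimum cut-off.

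The second reply concerns size. A reader might infer that cases must be few because participants feel healthy and known diabetes and thyroid disease are excluded, and so expect an excess of 10 points or more. The documents do not support that. They give no case numbers, and both the Background and the Discussion describe the target disorders as common in the elderly. With several hundred cases the excess is about 2 points.

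The third reply is that the gray zone is not much affected. A reader might extend the criticism to those limits, but limits set at a fixed high sensitivity or specificity are nearly unbiased unless cases are very few. This stands, and the point is confined to the optimum cut-off.

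**Conclusion.** The point holds in conditional form. With one cohort and no stated correction or validation sample, the procedure in section 2.7 overstates sensitivity at the optimum cut-off, and the likelihood ratios with it. Specificity moves by half a point or less at N = 1467. The excess in sensitivity is about 10 points with 20 cases, 4 to 5 with 73, 3 with 147 and 2 with 293. It therefore matters below roughly 75 cases and becomes minor at several hundred. These figures rest on binormal markers of equal variance, a Youden cut-off and AUC 0.70 to 0.80, none of which the article states.

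Two stronger readings should be avoided. The article does not declare uncorrected same-sample evaluation, so it cannot be said that the published figures are bound to be too favourable; they will be unless corrected. Nor does section 2.7 promise decision limits: its wording is tentative, and only the Discussion is firm. The aim is secondary and the primary reference intervals are untouched, so this is a moderate recommendation.

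**What to change.** Add a short statement to the analysis plan for the diagnostic aim:

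- Name the criterion that defines the optimum cut-off, and the target values for the high-sensitivity and high-specificity limits.
- Reselect the cut-off within each bootstrap resample, and reselect the marker too if several are compared.
- Report optimism-corrected sensitivity, specificity, predictive values and likelihood ratios as the main figures, with a bootstrap interval for the cut-off itself.
- State the number of cases beside every result, label uncorrected values as apparent, and call the cut-offs exploratory pending external validation.

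No new data or recruitment is needed. The cost is a short script beyond the two named packages and slightly less favourable accuracy figures. The correction removed about 70% of the optimism in the setting checked, so corrected values remain a little optimistic, which is a further reason to keep the exploratory label.
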